The second stage of enrollment is at the resident level. Participants must be (1) able and willing to provide verbal informed consent, (2) at least 18 years old, (3) able to communicate in English or Spanish, (4) living in the building at least 5 days/week and 9 months/year, and (5) not planning to move in the next 2 years. Participants who (1) have severe physical or mental medical conditions (e.g., cognitive disability) or other factors that could limit participation or ability to give informed consent in the study at baseline or during follow-up visits, (2) participate in focus groups conducted pre or concurrently as RCT that are geared towards understanding how to improve intervention arms for greater impact (buildings identified for focus groups are buildings that will not be assigned an intervention or have recruitment conducted for the main study), or (3) only smoke non-tobacco products (e.g., marijuana) are excluded from participating in the study due to the focus of the study on tobacco products. It should be noted that during the period of recruitment, the smoke-free policy in NYCHA was modified to also include marijuana use. In anticipation of this modification to the smoke-free policy, we are collecting preliminary information regarding marijuana use.

Recruitment of NYCHA residents will be conducted via door knocking and lobby intercepts until the targeted number per group is reached (4 smokers, 4 non-smokers in each building). Smoker status is defined as smoking a tobacco product including e-cigarettes at least 5x/month, and nonsmoker status is defined as never having smoked any product or quit smoking at least 12 months prior to recruitment.

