### Outcomes {12}

#### Primary Outcomes:

There are three primary outcomes being measured:

We will evaluate the change in number of cigarettes smoked per day using self-reported average number of cigarettes smoked per day among smokers measured at the time of baseline assessment, interim assessment (approximately 3 months post-intervention), and long-term assessment (approximately 12 months post intervention).We will evaluate change in salivary cotinine levels for 25% of the sample via passive drool collection among smokers and non-smokers collected at baseline assessment and the long-term assessment.We will evaluate change in secondhand smoke exposure via self-reported amount of exposure to secondhand smoke. This will be measured in all three assessments.

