#### Sample Size {14}

Power analysis was conducted using software PASS.15 for the primary outcome (change in salivary cotinine over a year) in Aims 1 and 2. Sampling 16 clusters (buildings) with 4 subjects per cluster (smokers for Aim 1, non-smokers for Aim 2) in each arm, we have 128 subjects per group or 256 in groups with or without a specific type of treatment (e.g. resident endorsement vs. no endorsement, cessation vs. no cessation). We calculated effect size as group mean difference in unit of standard deviation (SD) of the outcome, based on a two-sided test for mean difference between two groups in a cluster-randomized design with power of 80%. To compare groups with and without specific type of treatment, the group size of 256 may detect effect size of 0.283SD, 0.299SD, 0.312SD at significance level alpha = 0.05 for intra-cluster correlation coefficient r = 0.1, 0.15, 0.2, respectively. To compare intervention arms to the control arm, we have 3 comparisons and use conservative Bonferroni adjustment for multiple tests on significance level that alpha = 0.0167 (= 0.05/3). The sample size of 128 subject per arm may detect effect size of 0.472SD, 0.499SD and 0.524SD for r = 0.1, 0.15 and 0.2, respectively, at alpha = 0.0167. To put these numbers in perspective, using mean and SD estimated from a study of smokers in Maryland, an effect size of 0.283SD would correspond to a mean difference in salivary cotinine between the two intervention groups of 55.3 ng/mL with group SD = 195.4 ng/mL for smokers and of 0.19 ng/mL with group SD = 0.672 ng/mL for non-smokers.124 For instance a mean difference in 5 cigarettes smoked per day in the same study was 59.6 ng/mL for smokers.124 In England, following the smoke-free legislation salivary cotinine declined from mean level of 0.36 to 0.07 ng/mL (mean difference 0.29 ng/mL) among non-smokers.125 These findings support that we have sufficient power to estimate the impact of our interventions. The study is powered on an 80% retention rate, which we have achieved in other studies. Reasons for attrition will be tracked; those lost to follow up will be compared to the final sample.

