#### Plans for collection, laboratory evaluation and storage of biological specimens for genetic or molecular analysis in this trial/future use {33}

Exposure to smoke either directly among smokers or indirectly through secondhand smoke will be assessed through self-report and salivary collection.

We will collect saliva for 25% of recruited individuals from each building on a rolling basis at baseline and at 12 months via passive drool collection. Donors tilt their head forward, allowing the saliva to pool on the floor of the mouth, then pass the saliva through the SalivaBio Collection Aid (SCA) into a polypropylene vial. Collection protocols/methods are available online at www.salimetrics.com or upon request (Salimetrics Cotinine ELISA Kits). Saliva cotinine will be measured at the Columbia University Biomarker Core Laboratory directed by [name] using cotinine ELISA Kits (Salimetrics, State College, PA). The Salimetrics ELISA kit is an enzyme immunoassay used to measure primary or secondhand exposure to nicotine via cotinine. It is not intended for diagnostic use. It is intended only for research use among humans and some animals. The assay is non-invasive, involves no genetic sequencing, and is not used as a diagnostic procedure.

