### Primary outcome

1)

Self-reported average number of cigarettes smoked per day and secondhand smoking exposure (hours of secondhand smoke exposure in the building in the past 7 days) will be measured at baseline (in person interview), 3 months (phone interview) and 12 months (in person interview). Salivary cotinine will be measured for 25% of the sample at baseline and at the 12-month follow-up for smokers to evaluate reliability of self-reported smoking behavior in Aim 1 and for non-smokers to evaluate self-reported secondhand smoke exposure in Aim 2.

To examine the intervention group differences in the change of self-reported smoking (Aim 1), we will use GLMRM with identity link, E(Yijkh) = ßh + ßkhtk + ßZij, where Yijkh is an outcome variable (transformed if necessary) for smoking exposure measured at time tk (t0 = 0 for baseline; t1 = 1 for 6 months, 0 else; and t2 = 1 for 1 year, 0 else) from the ith participant of the jth building in the hth arm/group (h = 1, 2, 3, 4). For the reference group of h = 4, ßk4 = 0 for k = 0, 1, 2; so that parameter ßkh (k = 1, 2; h = 1, 2, 3 for intervention arm) indicates the difference in outcome change since baseline between intervention group h and reference group, and ß is a vector of coefficients for the vector of control variables Zij (if any). To examine if effect of treatment A depends on treatment B or vice-versa, we will test null hypothesis ßk1 = ßk2 + ßk3 for all k, which suggests independent effects of treatment A and treatment B and simpler model that E(Yijk) = ß0 + ß1A + ß2B + ßk0tk + ßk1tk A + ßk2tk B + ßZij with dummy variables A and B indicating treatment type. To examine the intervention group differences in the change in hours of secondhand smoke exposure in the building in the past 7 days for non-smokers, we will use GLMRM with log link (Aim 2). Models will be run with and without control variables (if any).

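### The non-smoker definition does not rule out unsmoked nicotine, which the cotinine assay cannot tell from secondhand smoke, and the sampled groups are small enough for one such person to matter

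*Protocol article*

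**What the plan says.** All references are to the protocol article.

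- **Strata.** Eligibility Criteria {10} defines both groups by smoking. For the non-smoker stratum the rule reads: "nonsmoker status is defined as never having smoked any product or quit smoking at least 12 months prior to recruitment". The smoker stratum takes in e-cigarette users and has a threshold of five uses a month. The participant criteria exclude people who smoke only non-tobacco products. They say nothing about smokeless tobacco or nicotine replacement among non-smokers.
- **Assay.** The biological specimens section {33} describes the test as "an enzyme immunoassay used to measure primary or secondhand exposure to nicotine via cotinine".
- **Role of cotinine.** The primary outcomes under Outcomes {12} include: "We will evaluate change in salivary cotinine levels for 25% of the sample via passive drool collection among smokers and non-smokers". Sample Size {14} opens: "Power analysis was conducted using software PASS.15 for the primary outcome (change in salivary cotinine over a year) in Aims 1 and 2", and translates the detectable effect into "0.19 ng/mL with group SD = 0.672 ng/mL for non-smokers". The Primary outcome paragraph of the statistical methods gives non-smoker cotinine another job: "for non-smokers to evaluate self-reported secondhand smoke exposure in Aim 2". The sensitivity analyses then plan a regression calibration for imperfect self-report.
- **Sampling.** Saliva is taken from 25% of participants (n = 128) at baseline and at the final follow-up {18a}.
- **Transformation.** Skewed continuous variables are to be transformed only if that proves necessary {20a}.

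**The concern.** The eligibility rule is about smoke, while the measurement is about nicotine. Someone who gave up cigarettes two years ago and still uses nicotine gum, or who uses smokeless tobacco and has never smoked, qualifies as a non-smoker as the rule is worded. That person's cotinine mostly reflects their own nicotine intake, not smoke from neighbouring apartments.

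Two uses of the data are exposed. First, the non-smoker cotinine comparison could turn on whether a group happened to include such a person and how that person's use changed over the year. Second, the check of self-reported exposure against cotinine, and any calibration built on it, would treat a correct report of little secondhand smoke as an error. With so few saliva samples per group, randomisation cannot be relied on to balance one or two such people.

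**Working it through.** **Inputs from the protocol article.** Detectable effect 0.283 SD for groups with versus without a treatment, and 0.472 to 0.524 SD for an arm against control; non-smoker SD 0.672 ng/mL {14}. 512 participants, half of them non-smokers, in four arms {8}. Saliva from 128 people {18a}.

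**Assumptions, not in the document.** Saliva is split evenly by stratum and arm. A nicotine user among the non-smokers has cotinine of 50 to 200 ng/mL. For scale only, Sample Size {14} gives smokers an SD of 195.4 ng/mL and a difference of 59.6 ng/mL for five cigarettes a day. That user's level changes by 20% between the two samples. The share of users among enrolled non-smokers is 0.5% to 5%.

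**1. The plan's own figure.** 0.283 × 0.672 = 0.190 ng/mL. This reproduces.

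**2. Non-smokers with saliva.** 128 / 2 = 64 in all, 64 / 2 = 32 per pooled group, and 64 / 4 = 16 per arm.

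**3. Change in one person that moves the mean change by the target.** The shift in a group mean is (one person's change) / n.
- Pooled group: 0.19 × 32 = 6.1 ng/mL. At 80% retention, n = 25.6 and the figure is 4.9 ng/mL.
- Single arm, against the arm-level effect: 0.472 × 0.672 = 0.317 ng/mL, and 0.317 × 16 = 5.1 ng/mL.

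**4. An assumed user whose level changes by 20%, pooled group.**

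| Level (ng/mL) | Change | Shift in mean change (÷ 32) | Multiple of 0.19 |
|---|---|---|---|
| 50 | 10 | 0.31 | 1.6 |
| 200 | 40 | 1.25 | 6.6 |

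A user whose level does not change contributes zero to the mean change.

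**5. Effect on spread.** Take 0.672 as the SD of change, as the power calculation does. One deviation of 10 ng/mL among 32 people gives SD = √[(30 × 0.672² + 10² × (1 − 1/32)) / 31] = 1.9. Then 0.19 ng/mL is 0.10 SD, not 0.283 SD.

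**6. Chance of at least one user among the 64 sampled.** 1 − (1 − p)^64 is 27%, 47%, 73% and 96% for p = 0.5%, 1%, 2% and 5%.

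**The case against.** Several arguments on the other side have force.

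- **Overlap of the two definitions.** A reader might infer that a former cigarette smoker who vapes weekly falls into both strata. The text does not show this. Weekly use is 52 / 12 = 4.3 times a month, below the threshold of five, and the smoker definition counts e-cigarettes as smoking. On that reading a current vaper has not quit. What remains is uncertainty about where lighter e-cigarette users belong.
- **Planning figures.** A reader might infer that the SD of 0.672 ng/mL comes from people with no nicotine intake, so that the criteria contradict the power calculation. Sample Size {14} does not say how its source defined non-smokers.
- **Level against change.** It is tempting to divide one user's cotinine level by an arm's 16 samples and set the result against 0.19 ng/mL. That mismatches twice: the outcome is change, and 0.19 ng/mL belongs to pooled groups.
- **Existing protection.** A transformation would greatly reduce one person's leverage. However, it is conditional, the 0.19 ng/mL is on the raw scale, and no transformation turns nicotine replacement into secondhand smoke. The study also reassures residents that interviewers do not represent the housing authority, and it measures social desirability. Both help honest reporting of smoking, but neither touches unsmoked nicotine.
- **Left to other documents.** A cotinine cut-off is ordinary analysis-plan content, so its absence from an article is not itself a fault. The eligibility wording is stated here, however, and it is the wording that admits these people.
- **Limited role.** The Aim 2 model uses self-reported hours, and the 0.19 ng/mL is offered as perspective. Even so, Outcomes {12} lists cotinine as primary and Sample Size {14} is built on it.

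**Conclusion.** The concern holds in a bounded form. As worded, the non-smoker definition can admit people whose cotinine does not measure secondhand smoke, in a trial where that cotinine is a primary outcome, the basis of power and the check on self-report. Given an even split of saliva, a change of about 6 ng/mL in one of 32 people equals the whole 0.19 ng/mL. Under the assumed levels and a 20% change, the shift is 1.6 to 6.6 times that effect.

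The prevalence of such users, their levels and how much those levels change are all assumptions. The documents do not support saying that any one nicotine user will swamp the result, because a stable user leaves the mean change untouched. The case for acting is that the gap is plain in the text and cheap to close.

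**What to change.** 1. Define a non-smoker as someone who has used no tobacco or nicotine product, including e-cigarettes, smokeless tobacco and nicotine replacement, in the 12 months before recruitment. Recruitment is described as under way, so apply this from now on and put the same question to those already enrolled.
2. Before unmasking, fix a baseline cotinine limit that indicates active nicotine use. Leave sampled non-smokers above it out of the non-smoker cotinine analysis and the calibration, and report an analysis that includes them as sensitivity. Baseline saliva is collected before the intervention starts, so this rule does not select on an effect of treatment.
3. Record nicotine product use at each assessment, so that use begun after baseline is visible.

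The cost is one or two questions, a rule applied to samples already being collected, and the loss of a few people from an already small cotinine set. It does not cure the low power of the 25% subsample. With 32 per group and no allowance for clustering, 0.19 / (0.672 × √(2/32)) = 1.13, which gives about 20% power at two-sided 0.05 even with no nicotine users present.

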### Who Will Take Informed Consent? {26a}

Participant contact will be done face-to-face with systematic questionnaires and potentially identifying information will be asked or recorded for study participants (although NO birthdates, photos, or video recordings will be taken of participants) by trained field research support staff. Consent to participate in the study will be asked before the actual study begins and individuals who refuse will not take part in the study. We will explain the study, its intent, its potential risks, and ask if we can proceed. Informed consent documents and study materials will be translated (forward and back translated) and administered in Latin Spanish where needed. Any information that is collected and is recorded first on paper will then be entered into a computer and transferred and stored in a secure electronic environment. Upon conclusion of the study, all identifying information for each participant will be destroyed.

Additionally, a waiver of written documentation of informed consent has been obtained through the overseeing IRB as the research presents no more than minimal risk of harm to subjects and does not involve procedures for which written consent is normally required outside of the research context. A waiver of documentation of consent is appropriate because the only link between the subject and the study would be the consent document and the primary risk is a breach of confidentiality.

### Additional Consent Provisions For Collection And Use Of Participant Data And Biological Specimens {26b}

The study data will be released to the funder, the National Institutes of Health (NIH) and National Cancer Institute (NCI) at the conclusion of the study. Identifiers will be removed and, after such removal, the information or biospecimens could be used for future research studies or distributed to another investigator for future research studies without additional informed consent, as appropriate.

## Interventions

### Explanation For The Choice Of Comparators {6b}

Buildings and study participants assigned to the comparator arm [Arm 4] are recruited and followed over approximately a 12-month period to assess outcomes. No additional programs or services will be delivered to the buildings or residents assigned to this arm beyond standard programs that NYCHA may provide to support the smoke-free mandate. Field staff will document any policy-related signage, activities, or information to which these participants are exposed. We expect and have confirmed that Smoke-Free NYCHA’s liaison program will occur during our period of data collection during which they will conduct programming and activities that support compliance to the smoke-free policy. As such, the buildings enrolled in our ‘Standard NYCHA approach’ are buildings that the Smoke-Free NYCHA team has identified as locations for concentrated efforts of their own smoke-free programming over the course of our data collection period. We will therefore evaluate the impact of this parallel prevention program including a covariate for NYCHA study participation at baseline in the models specified below. We will further allow for an interaction between the NYCHA study participation indicator and the treatment group.

### Intervention Description {11a}

The development of the interventions is grounded on prior smoke-free policy endorsement and tobacco reduction/cessation programs. NYCHA conducted a smoke-free pilot project in 2015 centered on a smoke-free home pledge at a housing complex in Upper Manhattan (67). The initiative was organized by members of the tenant association and entailed families and neighbors taking a voluntary pledge to maintain a smoke-free living environment. The overwhelming majority of residents (85%) signed the pledge, including nine floors in which all apartments took the pledge. At a culminating celebration, residents shared personal accounts of motivations for endorsing a smoke-free living environment (67). Several elements of the “resident endorsement” intervention arm are fashioned after this pilot initiative, including fostering social connections between residents, providing information on the hazards of smoking and secondhand smoke along with the pledge culminating in a town hall session.

For the “reduction/cessation” intervention arm, [name], DDS, has led and directed the design of the tobacco cessation protocol. He also provided the foundational tools and trainings necessary to effectively use motivational interviewing to not only support smoking cessation, but also to reduce personal smoking. [name] expertise comes from implementing and evaluating evidence-based tobacco cessation programs at the New York Presbyterian (NYP) Cornell and NYP Columbia campuses and within affiliated community-based organizations, including many that engage minority populations. At NYP Hospital he is the Tobacco Cessation Project Lead for the Medicaid Redesign Project funded by the NYDOH Delivery System Reform Incentive Payment Program. This program trains clinicians through a certified tobacco cessation specialist program, implements tobacco cessation counseling and offers community presentations and engagement. As the Co-PI for the NCI funded Tobacco Cessation via Public Health Dental Clinics, he has examined the effectiveness of brief office- based interventions designed to assist patients quitting smoking or smokeless tobacco use. [name] is the co-Project Lead of the Development of a Tobacco Cessation Program for Cancer Patients at Columbia University. The project aims to implement an evidence-based tobacco cessation program for smoking patients at the Columbia University Herbert Irving Comprehensive Cancer Center.

To further enhance the intervention curriculum, we have conducted key informant interviews with residents and experts in resident engagement, tobacco cessation and housing-based health interventions. These interviews were designed to elicit strategies to not only improve the RCT approach, but also to ascertain necessary adaptations to the intervention protocols to maximize their efficacy. Such discussions led to expanding the scope of the reduction/cessation intervention which previously was designed to focus on relocating smoking and cessation only. Furthermore, our community partner, Health People have previously conducted health education activities in similar settings and their expertise in resident facing activities will further enhance resident engagement.

Prior to the implementation of the intervention, recruitment and baseline data collection via survey questionnaire, passive drool sample collection and sensory building observations will be conducted. Trained study staff will obtain verbal consent upon the time of recruitment and data collection prior to enrollment in the study. Approximately a month after this completion, interventions will be implemented by peer educators in accordance with respective building assignments.

#### Arm 1: Reduction (via relocation and reduction in personal smoking)/Cessation

The reduction/cessation arm (Arm 1) “meets smokers where they are” using a) a harm reduction approach that reinforces the use of designated smoking areas available and/or identifies ways residents can reduce their personal smoking more generally via motivational interviewing skills thereby encouraging compliance via relocation and personal smoking reduction; along with b) in-residence cessation support to reduce barriers to participation in cessation services. Enrolled participants who are smokers will be referred by the survey team to peer educators from Health People. The peer educator will coordinate smoking cessation support, including serving as a liaison between participant and research team, providing information regarding the smoke-free policy and opportunities for relocation, and connecting participant to tobacco replacement therapy and/or physician support if deemed appropriate.

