### Concealment Mechanism {16b}

The allocation of interventions is done on a building basis and will only be revealed to specific research team members and intervention implementors (PEs). This information will be passed to Health People via encrypted emails. All data collectors will not be informed of intervention assignment for the duration of the study.

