## Assignment of interventions: Blinding

### Who Will Be Blinded {17a}

Trial participants and outcome assessors are blinded after the assignment to interventions. All interventions are assigned at the building level. We have a separate field team research support staff who conduct recruitment and collect the assessments but are unaware of the assignments.

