## Data collection and management

### Plans For Assessment And Collection Of Outcomes {18a}

There are three assessments during this trial. These include a baseline assessment conducted upon recruitment and after building randomization, an interim assessment conducted over the phone approximately 3 months after the delivery of intervention, and a final long-term assessment conducted approximately 12 months after the delivery of intervention. The survey questionnaire collects information on housing conditions, indoor air quality, personal smoking behavior and cessation attempts, exposure to secondhand smoke, opinions on secondhand tobacco exposure, the smoke-free policy and tobacco policies, and health conditions. Additionally, passive drool samples from 25% of participants (n = 128) is collected at the time of the baseline assessment and at the final follow-up. Sensory building observations occur at the start of recruitment and during the final assessments to record signs of active smoking and/or tobacco/marijuana odor. The presence of cigarettes, cigars, ashtrays with/out ashes, matches or lighters will be documented within apartments and around the building premises including stairwells, elevators, hallways, laundry rooms, in/outdoor community spaces, playgrounds, and the perimeter of the buildings.

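### Referral of smokers by the survey team, written into the reduction/cessation arm, conflicts with the statement that data collectors do not know building assignment

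*Protocol article*

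**What the plan says.** In the protocol article, the Arm 1 section on reduction/cessation describes how a smoker reaches the intervention: "Enrolled participants who are smokers will be referred by the survey team to peer educators from Health People". The Arm 3 section delivers the same treatment alongside resident endorsement, so the referral step carries over to that arm. The Arm 2 section describes no such referral. The section on the choice of comparators says the control arm receives nothing beyond what the housing authority itself provides.

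The blinding statements are firm. Under Concealment Mechanism {16b}: "All data collectors will not be informed of intervention assignment for the duration of the study". The same section restricts knowledge of the allocation to certain research team members and the peer educators. Under Who Will Be Blinded {17a}: "Trial participants and outcome assessors are blinded after the assignment to interventions", and then "We have a separate field team research support staff who conduct recruitment and collect the assessments but are unaware of the assignments". The section on unblinding {17b} repeats that a building's assignment is withheld from data collectors. It concedes only that they might guess it from what is or is not on display.

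Two of the three primary outcomes rest on what participants tell an interviewer: "self-reported average number of cigarettes smoked per day among smokers" and the self-reported amount of secondhand smoke exposure.

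**The concern.** A person who refers smokers in some buildings and not in others knows which buildings have the cessation component. If that person also conducts the follow-up interviews, assessor blinding is lost on that contrast through a planned task of the protocol, not through an accident.

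Interviewers take the self-reported outcomes by phone at 3 months and in person at 12 months. An interviewer who knows that a smoker was referred for help to cut down may probe or record differently. The participant may also answer differently to someone who arranged that help. Either would bear on comparisons of a cessation arm with control, and on the comparison of buildings with and without cessation, which the sample size section treats as a main contrast. The protocol's section on interviewer bias names blinding as one of its safeguards, so a procedure that undoes it deserves correction.

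**Working it through.** No arithmetic in the plan bears on this point apart from a count of buildings. The check sets the sections side by side.

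1. **Who refers?** The survey team (Arm 1 section). The term is not defined in the article.
2. **Who collects survey data?** The consent section {26a} says "Participant contact will be done face-to-face with systematic questionnaires" and assigns this to trained field research support staff. The Implementation section {16c} has field-based research support staff recruiting and enrolling. The section on who is blinded has field research support staff recruiting and collecting the assessments. These three sections describe one kind of staff, and no second survey-collecting team appears. Reading the survey team as the blinded field staff is therefore a strong inference, though the article does not state it.
3. **Where does referral apply?** It appears only in the Arm 1 description and, through the combined intervention, in Arm 3. Arms 2 and 4 have no use for it.
4. **What would arm-specific referral reveal?**

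| Arm | Cessation component | Smokers referred | Buildings |
|---|---|---|---|
| 1 Reduction/cessation | yes | yes | 16 |
| 2 Resident endorsement | no | no | 16 |
| 3 Combined | yes | yes | 16 |
| 4 Standard approach | no | no | 16 |

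Buildings with referral: 16 + 16 = 32 of 64. Buildings without: 64 − 32 = 32. Since the absence of referral is also informative, all 64 buildings could be sorted into cessation and no cessation. Referral does not separate Arm 1 from Arm 3, or Arm 2 from Arm 4. With 4 smokers per building, the referrals would cover 32 × 4 = 128 smokers.

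5. **When?** No section dates the referral. It has to precede cessation support, and the follow-up assessments come about 3 and 12 months after delivery, so both follow it. Baseline is less clear. The assessment section describes "a baseline assessment conducted upon recruitment and after building randomization", so the allocation already exists at that time. But the Intervention Description {11a} starts the interventions about one month after recruitment and baseline are finished, so referral may fall after both.
6. **Does the admission under {17b} cover it?** No. That section allows for guessing from displayed materials. Referral is an assigned task and is not mentioned there.
7. **Do other safeguards cover it?** In part. The section on interviewer bias provides structured questionnaires, standard probes, items on social desirability and interviewers who do not know the hypotheses. Cotinine is measured in 25% of participants (128 of 512, or 128 / 64 = 2 per building), at baseline and 12 months only. It gives no check at 3 months and leaves three quarters of the sample on self-report alone.

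**The case against.** The strongest reply is that blinding can survive the sentence as written. The peer educators already hold the allocation, and the sentence speaks of enrolled smokers without limiting them to certain buildings. The survey team might pass on every smoker, whose status it records anyway to fill the quota, and leave the peer educators to act only where assigned. Placement under Arm 1 would then merely reflect which intervention uses the list. This is possible, and it is why the point is conditional. But the article does not say it, and a step described only within one arm's procedures is naturally read as belonging to that arm. If it is the practice, one sentence settles the matter.

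A second reply is that the survey team may be a different group, or may include an office-based coordinator. The article does not exclude this, but it describes no such group. A third is that an article condenses its workflow. That would excuse silence; here the text names a team for the referral and describes the same kind of staff as unaware of assignment.

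A fourth is that participants may know what they receive, so the interviewer's knowledge adds only a secondary bias. That is fair, and it limits the importance of the point. It does not remove it, since assessor blinding is the part that the trial can control.

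A reader might also infer that arm knowledge shaped who was recruited to quota or how baseline answers were taken, because both follow randomization of buildings. The documents do not support this. Referral concerns people already enrolled, its date is not given, and the concealment section denies recruiters prior knowledge of the allocation.

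**Conclusion.** The referral procedure and the blinding statements need to be reconciled. Followed as its placement implies, the referral lets interviewers distinguish the 32 buildings with a cessation component from the other 32 before the 3- and 12-month self-reported primary outcomes. This rests on two assumptions: that the survey team is the field staff described as blinded, which is a strong inference, and that referral is made only in Arms 1 and 3, which the text implies without stating.

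Two stronger readings go too far. One is that assessors learn the exact arm: referral does not separate Arm 1 from Arm 3. The other is that 32 buildings are unmasked from baseline: the timing is not stated. The direction and size of any reporting bias cannot be derived from the document, and the safeguards already in place reduce the risk without removing it. The point merits correction because the remedy is nearly free, not because bias has been shown.

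**What to change.** In the Arm 1 section, and by reference in Arm 3, replace the direct referral. The survey team sends the list of enrolled smokers from all 64 buildings (64 × 4 = 256 at full recruitment), in the same format and at the same point in each building's schedule, to a research team member who already holds the allocation. That person alone forwards the Arm 1 and Arm 3 smokers to the peer educators. Whatever interviewers tell smokers about possible later contact should be identical in every building.

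Under Who Will Be Blinded {17a}, add that data collectors make no arm-specific referral. If smokers from all buildings are already passed on without regard to arm, stating that is enough.

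The cost is two sentences and a small list-transfer step. The concealment section shows that staff holding the allocation already exist, so no new post is needed. Design, sample size and analysis are unchanged.
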